## Abstract

**Background:**

Empirical evidence pertaining to the influence of treatment preferences on attrition, adherence and outcomes in intervention evaluation trials is inconsistent. The inconsistency can be explained by the method used for allocating treatment and measuring preferences. The current methodological study is designed to address these factors by implementing the two-stage partially randomized or preference trial design, and administering a validated measure to assess participants’ preferences for the treatments under evaluation. It aims to compare attrition, adherence and outcomes for participants allocated randomly or by preference to treatment. The study is in its final stages of data collection; its protocol is presented in this paper.

**Methods/Design:**

A partially randomized clinical or preference trial is used. Eligible participants are randomized to two trial arms. First is the random arm involving random assignment to treatments, and second is the preference arm involving allocation to the chosen treatment. Participants with chronic insomnia are targeted. Two behavioral treatments are offered, stimulus control therapy and sleep restriction therapy, in the same format (small group) and dose (two sessions given over a 4-week period). A participant log is used to collect data on attrition. Adherence is evaluated in terms of exposure and enactment of treatment. Sleep-related outcomes (sleep parameters and perceived insomnia severity) are measured at pretest, posttest, 6 and 12 month follow-up. Treatment preferences, adherence and outcomes are assessed with reliable and valid measures.

**Discussion:**

The advantages and limitations of the preference trial design are highlighted. The challenges in implementing the trial are discussed relative to the distribution of participants in the groups defined by treatment received and method of treatment allocation.

**Trial registration:**

ClinicalTrials.gov Registry NCT02513017

## Background

Treatment preferences represent people’s choice of therapy [1]. Treatment preferences contribute to attrition, adherence and outcomes of treatment [2] and they can jeopardize validity [3] in intervention research. The empirical evidence pertaining to the influence of preferences on attrition, adherence and outcomes is inconsistent. In addition to differences in treatments and target populations, two methodological factors could explain the inconsistency in findings: the method used to assign participants to treatment and the measure used to assess treatment preferences. The current study, which is in its final stage of collecting follow-up data, is designed to address the methodological factors. This is accomplished by (1) implementing the two-stage partially randomized or preference trial design, which involves two methods (random and preference-based) of assignment to treatment and hence, facilitates the examination of the influence of treatment preferences on attrition, adherence and outcomes [4] within and across treatment groups; and (2) administering a validated measure to assess participants’ preferences for the treatments under evaluation.

This paper describes the study protocol for conducting the two-stage partially randomized clinical or preference trial. The paper begins with an explanation of the rationale for the study. The trial protocol is described, and challenges in its implementation are presented. The advantages and limitations of the design are also discussed.

The influence of treatment preferences on attrition, adherence, and outcomes has been investigated in several studies evaluating medical, behavioral and educational interventions for a variety of clinical conditions. The studies’ findings were synthesized in systematic reviews and meta-analyses. Overall, they point to inconsistencies as summarized next.

Three individual studies [5–7] and one systematic review [8] reported comparable attrition rates for participants who received treatment that did and did not match their preference. However, the results of two studies [7, 9] and two meta-analyses [10, 11] showed lower attrition rates for the matched than the mismatched subgroups, implying that participants who received their preferred treatment were less likely to withdraw from the trial.

The results of five individual studies were consistent in showing that assignment to treatment, matched to participants’ preferences, is associated with enhanced adherence operationalized as attendance at treatment sessions [9, 12–14] or engagement in treatment activities [15]. In contrast, the findings of the two systematic reviews did not support the relationship between preferences and adherence [16, 17].

The findings of one systematic review [8] and two meta-analyses indicated that participants allocated to the preferred treatment demonstrated greater improvement in outcomes than those randomized to the non-preferred treatment. The mean effect size (Cohen’ d coefficient) ranged between .15 [95 % confidence interval: .01–.31] [10] and .31 [95 % confidence interval: .20–.43] [11]. In contrast, Gelhorn and colleagues [16] concluded that preferences had minimal impact on the outcomes.

Conceptual and methodological factors could have contributed to the inconsistent findings and the small-to-moderate effect sizes quantifying the impact of treatment preferences on outcomes. These factors include differences in the characteristics of the target populations (e.g. patients with depression or heart disease), the types of treatment under investigation (e.g. medical, behavioral), the context of treatment implementation (e.g. institution, home), the method of allocation to treatment, and the method for assessing preferences. The latter two methodological factors are of concern because they could have attenuated the estimates of the association between preferences and outcomes and they can be addressed in future research aimed to evaluate the influence of treatment preferences. Most previous studies consisted of randomized clinical trials in which participants, whose preferences were assessed at baseline, were randomized to treatment groups. The random method of assignment ignored participants’ preferences; however, these preferences were accounted for at the stage of data analysis by generating a match-mismatch (i.e. whether the received treatment was congruent with the preferred treatment) between-subject factor. The extent to which active involvement of participants in treatment selection and allocation to the preferred treatment make a difference in attrition, adherence, and outcomes has not been extensively investigated.

In the majority of trials reviewed, the method for assessing preferences consisted of administering one item inquiring about participants’ choice, which has three limitations. First, the use of one item, with no demonstrated psychometric properties, could have introduced measurement error, raising questions about the accuracy of the expressed treatment preference in reflecting participants’ choice. Second, the trials’ reports provided minimal details regarding the treatment-related information presented to participants prior to eliciting their preferences, and the format in which such information was given. The content and format for presenting treatment-related information affect participants’ perception of the treatment options [18–20].

Third, single items do not capture the complexity of treatment preferences, which are based on careful evaluation of the treatments’ attributes such as effectiveness, severity of side effects, and convenience of implementing the treatment in daily life [21–23]. Therefore, the method for assessing preferences has to be systematic in order to obtain well-informed and accurate expressions of participants’ preferences.

The two methodological factors were addressed in the current study. The method of allocation to treatment was examined by applying the two-stage partially randomized clinical trial [4] that involved two methods of allocation: random and preference-based. A systematic method, operationalized in the Treatment Acceptability and Preference scale [24], was followed to assess treatment preferences.

The goal of the current study was to clarify the contribution of treatment preferences in intervention evaluation research. The specific study objectives were:To compare participants randomized to treatment and participants allocated to the preferred treatment on: attrition, adherence to treatment, and outcomes.Among randomized participants, to compare those who received matched (i.e. congruent with expressed preferences) and those who received mismatched (i.e. incongruent with expressed preferences) treatment on: attrition, adherence to treatment, and outcomes.

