The sample size is estimated to attain adequate power to determine the effects of treatment preferences on attrition, adherence, and sleep outcomes. Sample size estimation also considers the repeated measure feature of the design. Within-subject designs require a smaller number of participants than between-subject designs, to achieve the same statistical power [30]. A medium sized effect (0.5) is anticipated on the basis of: 1) results of a systematic review showing that behavioral therapies had moderate-to-large effects on sleep parameters (sleep onset latency and wake after sleep onset) in middle-aged and older adults [31]; and 2) an expected medium effect for the comparison of participants assigned to treatment randomly or congruent with their preferences. A medium effect is anticipated, rather than a small effect as reported in the literature, with the use of a reliable and valid measure of treatment preferences. Applying Cohen’s [32] criteria for an anticipated medium effect size for the main comparison, the inclusion of four groups (i.e. participants allocated to the stimulus control therapy and those allocated to the sleep restriction therapy either randomly or based on their preference), and setting α at .05 and β at .80, the required sample size is 60 per group, for a total of 240 participants to be recruited.

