*Two components of adherence to treatment* are examined: exposure and enactment. Exposure is operationalized as participants’ attendance at the planned treatment sessions. The therapist facilitating the sessions records the presence of each participant and the total number of sessions attended will be counted. Enactment represents the extent to which participants apply the treatment recommendations in daily life. It is assessed by having participants complete a checklist. The checklist was developed following the procedure described by Stein and colleagues [33]. It includes 13 items reflecting the behavioral treatments’ recommendations that are discussed during the sessions and that participants are expected to carry out on a daily basis. Examples of these recommendations include: avoiding caffeine and nicotine before bedtime, going to bed only when sleepy and waking up at a regular time. Participants indicate whether or not they implement each of the listed treatment recommendations on every day of the treatment and post-test periods. They return the completed checklist along with the daily sleep diary every morning. The percentage of treatment recommendations actually applied, averaged by week, will quantify enactment.

*Sleep outcomes* include sleep parameters and perceived insomnia severity. The sleep parameters are assessed with the daily sleep diary (DSD) completed for a week, at each data collection point and during the 4-week treatment period. The DSD is a self-administered log of nightly sleep behaviors, developed by Morin [28]. Participants report on bed time, time to fall asleep, number and length of each awakening, and wake up time. They complete the DSD upon awakening and are asked to return the completed DSD by either calling in their responses to a voice mail service or sending them by e-mail, each morning to decrease the possibility of retrospective estimates and recall bias. The DSD demonstrated test-retest reliability (r: .69–.93) and validity, evidenced by correlation with actigraphy values for the same variables [27]. Relevant DSD data will be used to quantify the following sleep parameters: sleep onset latency (i.e. time it takes to fall asleep), wake after sleep onset (i.e. time awake across all awakenings), total sleep time, and sleep efficiency (i.e. percentage of total time in bed actually asleep).

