### Data analysis

In addition to descriptive statistics to characterize the participants in terms of their demographic and clinical characteristics, the following analyses are planned to address the study objectives:Objective 1: Chi-square test will be used to compare the number of participants who withdrew from the study across the four study groups defined by the type of treatment received (stimulus control therapy and sleep restriction therapy) and the method of allocation to treatment (random and preference). One-way analysis of variance will be applied to examine differences in level of adherence (i.e. attendance to treatment sessions and enactment of treatment recommendations), and the pattern of change (estimated with a slope) in the sleep outcomes, across groups.Objective 2: Chi-square test will compare the number of dropouts between participants in the random arm who receive matched and mismatched treatment. Independent samples t-test will examine differences between the matched and mismatched subgroups in levels of adherence (exposure and enactment) to treatment and the pattern of change in the sleep outcomes.

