Despite its advantages, there are some challenges in carrying out a two-stage PRCT. The first challenge relates to the first stage of randomization. Through the process of obtaining informed consent, participants are informed of the two stages and of the method for treatment allocation within each arm. Participants with strong treatment preferences may be unwilling to leave treatment choice to chance and they may desire allocation to the preference arm. If randomized to the random arm, they may react unfavorably [4] and withdraw from the study.

The second challenge in the implementation of the two-stage PRCT relates to the method of treatment allocation applied in the second stage of the trial. At this stage, participants in the random arm are randomized to treatment, yielding a balanced number of participants assigned to the treatment groups. However, the equality of the treatment groups’ sizes is not achieved in the preference arm if most participants choose one treatment over the other. Large differences in group sizes may yield unequal within-group variances; if not addressed with appropriate statistical formula, unequal variances may reduce the power to detect significant treatment and preference effects [35]. The validity of these conclusions is further jeopardized if the pretest comparability of participants is not maintained. Randomization to treatment, applied in the random arm, increases the likelihood of achieving baseline comparability. However, such comparability may not be observed in the preference arm due to possible differences in the profile of participants choosing the alternative treatments under evaluation. Therefore, the baseline comparability of participants assigned to the different treatments randomly or by preference is not maintained, potentially confounding the results.

The third challenge in conducting the two-stage PRCT relates to the reactions of participants assigned to treatment on the basis of chance or preference. Specifically, participants in the random arm may have preferences for the treatments under investigation. Those randomized to the non-preferred treatment may react unfavorably. In contrast, participants in the preference arm may react favorably because they get the treatment they desire. These reactions may influence the participants’ adherence and responses to the allocated treatment.

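### Analysis groups and match status are worded by therapy received, but the same groups are sized by therapy allocated; they should be fixed by assignment, above all for Objective 2

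*Protocol article*

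**What the plan says.** The article gives two rules for who belongs to which group.

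- **By receipt.** Objective 2, at the end of the Background, is "to compare those who received matched (i.e. congruent with expressed preferences) and those who received mismatched (i.e. incongruent with expressed preferences) treatment". Under Data analysis, Objective 1 is tested "across the four study groups defined by the type of treatment received" and by method of allocation. Objective 2 is tested between "participants in the random arm who receive matched and mismatched treatment". The Abstract's discussion paragraph uses the same phrase, "groups defined by treatment received and method of treatment allocation", but specifies no analysis there.
- **By allocation.** The Sample section counts the four groups as "participants allocated to the stimulus control therapy and those allocated to the sleep restriction therapy either randomly or based on their preference". Objective 1, in the Background, is also worded by how participants were randomised or allocated.

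On exposure, Variables and measures says: "The therapist facilitating the sessions records the presence of each participant and the total number of sessions attended will be counted". Two sessions are planned, so the score can be 0, 1 or 2. No sentence excludes people who attend none, and no sentence says that analysis follows assignment.

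The Discussion expects a reaction to the draw: "Those randomized to the non-preferred treatment may react unfavorably". It adds that such reactions may affect adherence and response.

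**The concern.** In the random arm the therapy is drawn from sealed envelopes. Among those who stated a preference at pretest, chance therefore decides who is matched, and a matched-versus-mismatched comparison is protected by randomisation. That protection holds only if match is defined by the draw. Receipt comes after the draw and may depend on it, for the reason the Discussion itself gives.

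Adherence is also an endpoint. Someone who attends no session shows the lowest possible exposure, yet has received neither therapy and so has no clear place in a grouping by receipt. An analyst who applies the wording literally would compare adherence only among people who had already adhered in part. For sleep outcomes, the same analyst would compare most of the matched group with a more selected part of the mismatched group. Another analyst, following the Sample section, would keep everyone. The two would build different datasets from the same article.

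**Working it through.** **1. The wording.** Objective 1 is worded by allocation in the Background and by receipt in Data analysis. The four groups are sized by allocation in the Sample section and analysed by receipt in Data analysis. Objective 2 is worded by receipt in both places where it appears. The plan has no figure of its own to reproduce on this point.

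**2. Inputs for an illustration.** The documents give no start rate, completion rate, share with a preference or correlation. All of these are assumptions.

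- Random arm: 2 × 60 = 120, from the Sample section.
- Share with a stated preference 80%, half of them matched: 120 × 0.8 / 2 = 48 per group (assumed).
- Probability of starting, s: 0.95 matched and 0.80 mismatched (assumed).
- Probability that a starter attends both sessions: 0.85 in both groups (assumed).

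**3. Exposure by assignment.**

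- Mean sessions = s × (0.15 × 1 + 0.85 × 2) = 1.85s.
- Mean square = s × (0.15 × 1 + 0.85 × 4) = 3.55s.
- Variance = 3.55s − (1.85s)².
- Matched: mean 1.758, variance 0.284.
- Mismatched: mean 1.480, variance 0.650.
- Pooled SD = √[(0.284 + 0.650)/2] = 0.683.
- d = (1.758 − 1.480)/0.683 = 0.41.

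**4. Exposure among starters only.** Both means are 1.85, so d = 0. This zero follows directly from assuming equal completion among starters.

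**5. Power.** In a simulated Welch t-test, 48 v 48 with everyone assigned gives about 50%. Starters only gives 4% to 5%, which is the chance level.

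**6. Other start rates.**

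| Starting, matched v mismatched | d by assignment | d among starters |
|---|---|---|
| 95% v 90% | 0.16 | 0 |
| 90% v 75% | 0.36 | 0 |
| 95% v 80% | 0.41 | 0 |

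**7. Sleep outcomes.** Let ρ be the correlation between the tendency to start and improvement. With no true effect, the bias among starters is ρ × [φ(z₂)/s₂ − φ(z₁)/s₁], where z is the normal quantile of 1 − s, group 1 is matched and group 2 is mismatched. At 95% v 80% the bracket is 0.350 − 0.109 = 0.241. The bias is then 0.048, 0.072 and 0.097 SD for ρ = 0.2, 0.3 and 0.4, in favour of the mismatched group. At 95% v 90% the bracket is 0.195 − 0.109 = 0.086, and the bias is 0.02 to 0.03 SD. For scale, the Background cites mean preference effects of 0.15 and 0.31.

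**The case against.** The strongest reply is that received simply means assigned in this article. The Design section speaks of people receiving the same therapy by chance or by preference as the result of the allocation scheme, and the Discussion uses receiving and being assigned for the same groups. This stands as evidence of what the authors may intend. It does not remove the explicit wording of the section that tells an analyst how to form the groups.

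A second reply is that attrition is compared across the same groups and counts every dropout after consent, so a person lost before the first session needs a group, which points to assignment. This has some force, but it is not decisive: dropout counted from consent also includes people lost before any randomisation, who fit neither rule.

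A reader might infer more than the text supports:

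- That non-attenders are removed and exposure is never scored zero. No exclusion is written, and the session count allows zero.
- That the trial is settled as an as-treated analysis. The wording is mixed.
- That participants who change therapy would be reclassified. No change of therapy is described.

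It is also fair to say that the numbers illustrate a mechanism and are not evidence about this trial, and that the direction of the sleep-outcome bias depends on assuming that starters have the better prognosis. Finally, a condensed article may leave formal analysis sets to a fuller document. The point here is not a missing definition but a stated rule that conflicts with another stated rule.

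**Conclusion.** The point holds as a conflict in how group membership is defined. It matters most for Objective 2, where match is randomised only if it is taken from the draw. Followed literally, the received wording would condition the adherence and sleep-outcome comparisons on attendance after randomisation.

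Whether this would happen, and how large the effect would be, cannot be known from the document. On the assumed start rates, the exposure difference lost ranges from d = 0.16 to 0.41, and the sleep-outcome bias is 0.02 to 0.10 SD. The exposure figures rest on equal completion among starters, and the sleep-outcome figures on a positive correlation of 0.2 to 0.4. If matched and mismatched participants start equally often, there is no such distortion. The change should be made because it is cheap and protects the randomised contrast.

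**What to change.** - In Objective 2 and in the Data analysis section, replace received with assigned, so that the groups agree with the Sample section and with Objective 1.
- Define match, among random-arm participants with a stated preference, as the therapy drawn at the second stage compared with the pretest preference.
- Keep every assigned participant in the exposure comparison, with a score of 0 if no session was attended. Group enactment by assignment too, and say how participants with no checklist are handled.
- Analyse available sleep data by assigned group. This reduces, but does not remove, bias from missing follow-up, because non-starters who return no later data are still absent.
- Report any as-received comparison as a sensitivity analysis only.

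The cost is wording and a few more records in the analysis. Assignment is known from the draw or the stated choice, and preference and attendance are already collected, so no new data or participants are needed. Mean adherence will look somewhat lower once non-attenders count as zero.
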